### Data Analytic Plan

#### Qualitative Analyses

Interviews will be transcribed verbatim, anonymized, and analyzed thematically using rapid qualitative analysis (RQA) [89,90]. RQA is the recommended method to conduct efficient qualitative analysis to address rapidly changing issues, such as modifying interventions to be culturally and contextually relevant in a timely manner [89,91]. The goal of RQA is to rigorously identify actionable data rather than in-depth and theoretical understanding [90]. Individual members of the investigative team summarize key findings and then audit the summaries to assess accuracy and display responses in a matrix. Responses are then discussed in team meetings to identify overlapping and divergent themes. A thorough description of the qualitative methods and findings from the initial qualitative interviews has been published previously by our team [64].

#### Quantitative Analyses

Quantitative analyses will be conducted to assess (1) within-participant treatment-related changes in emotion regulation and symptoms after participation in U-PEACE and (2) implementation outcomes, including treatment fidelity, acceptability, and implementation costs. We will examine missing data patterns, attrition rates, and distributional properties of measures and use transformations when necessary. Depending on patterns of missing data, analyses may use full maximum likelihood estimation, multiple imputation, and inclusion of covariates related to missingness to account for missing data.

Reliable change indices (RCIs) will be calculated by dividing the within-respondent differences in self-report and caregiver scores (ie, anxiety symptoms, depression symptoms, irritability, anxiety-related impairment, and academic problems) from baseline to after treatment by the SE for each measure [92]. RCI has previously yielded reliable estimates of clinically significant change over the course of treatment and can successfully analyze small sample sizes [93]. RCI >1.96 indicates clinically significant change throughout the course of the program—which would provide preliminary support that U-PEACE is impacting theoretical mechanisms and participants’ outcomes.

Furthermore, multilevel models will be evaluated to consider nesting of repeated measures (3 or 4 time points, depending on the measure) within participants, who are further nested within study conditions. School and U-PEACE group provider or providers will be included as predictors of intercept and slope to control for environmental differences between the groups. The best-fitting model for change over time will be determined for each dependent variable based on the Akaike Information Criterion and Bayesian Information Criterion. Time will be coded in weeks and will be “centered” alternately at treatment follow-up, such that model intercepts will represent mean scores at these assessments [94]. Treatment condition (ie, U-PEACE or SAU) will be entered as a predictor of the level 2 growth curve parameters (intercepts and slopes). These models will be used to assess group differences in both purported mechanisms of change (ie, emotion regulation measures) and in program outcomes (ie, symptom measures, academic outcomes, and diagnostic measures) as evidenced by slope or mean level differences at different time points.

Growth curve parameters will be used to categorize individual participants’ outcomes (as deteriorated, unchanged, improved, or recovered) by comparing them to each outcome measure’s clinical cutoffs and RCIs. Categorizations will be used to communicate findings to stakeholders and determine an appropriate range of participants for interviews after the RCT.

Implementation outcomes will be assessed using descriptive data, such as frequency of clinician adherence to U-PEACE components, participant’s homework completion, and participant’s session attendance. In addition, multilevel models (like those previously described) will be used to compare participants’ therapeutic alliance (TASC-R), program satisfaction (CSQ), and use of medication and supplemental services across study conditions.

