#### Recruitment

High school student participants will be recruited through staff referrals and community outreach. Students will also be able to express interest through QR codes on flyers posted throughout the high school campuses and on high school social media pages. Students can qualify for U-PEACE if they are aged between 13 and 18 years at the time of enrollment into the program and if they self-report clinically significant depressive symptoms (as indicated by scores at or above the clinical cutoff for the Patient Health Questionnaire-9, PHQ-9 [59,60]) or clinically significant anxiety symptoms (as indicated by scores at or above the clinical cutoff for the Generalized Anxiety Disorder-7 [61,62]). To qualify for U-PEACE, students will also need to be enrolled at one of the target high schools, want to voluntarily participate, and have a caregiver who will be available and willing to voluntarily sign their consent forms.

In addition to students who do not meet inclusion criteria, students will be excluded if their psychological symptomology is considered too severe to be effectively treated with a school-based prevention program, if they have neurological or medical conditions that may impact their ability to effectively participate in the group program, or if they do not speak or understand English or Spanish. During phases 2 and 3 of the study, students will also be excluded if they have a self-reported history of seizures, autism spectrum disorder, substance use disorder, serious mental illness, or other cognitive delay.

Staff members will be recruited to participate as support staff (eg, coach) through recommendations by individuals that participated in the qualitative interviews, clinic staff, or the administrators at participating schools. Staff at the target high schools will be excluded if they are not aged at least 18 years or are not able to speak and understand English fluently.

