#### Anxiety and Depression Symptoms

Adolescents’ anxiety symptoms will be measured using the Generalized Anxiety Disorder 7-item Scale (GAD-7) [61]. The GAD-7 will be used as both a self- and caregiver-report measure; the items in it are rated on a 4-point Likert-type scale that ranges from “not at all” to “nearly every day,” with higher scores suggesting more severe anxiety symptoms. While the authors are not aware of published psychometric properties on the parent-report GAD-7, the self-report GAD-7 has demonstrated good reliability in adolescent populations (Cronbach α=0.88) and has demonstrated strict measurement invariance by adolescents’ sex and grade, as well as good convergent and discriminant validity [62,79].

Adolescents’ depression symptoms will be measured using the PHQ-9 [59]. Items on the PHQ-9 scale are rated on a 4-point Likert-type scale that ranges from “not at all” to “nearly every day,” with higher scores suggesting more severe depression symptoms. The PHQ-9 has demonstrated good internal reliability (McDonald Ω=0.87) among adolescents, and confirmatory factor analysis for a 1D model suggested adequate fit [80].

There may be instances in which the research team chooses to administer a modified version of the PHQ-9 to adolescents and their caregivers. For instance, given that this measure may be administered remotely without the presence of a study team member, the Patient Health Questionnaire-8 (PHQ-8) may be used to ensure that any suicide-related concerns are handled immediately and in person by the research team [60]. Research has suggested that omitting the suicide item on the PHQ-9 has minimal impact on scoring [81]. The correlation between the PHQ-9 and PHQ-8 remains high; therefore, the cutoff scores remain unchanged [60,81]. While the authors are not aware of published psychometrics for parent-report PHQ-8, research on the general population suggests good sensitivity and specificity [60].

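### The reliable change index (RCI) uses an unspecified SE that, read literally, is too small by √2; RCI >1.96 is then called clinically significant and credited to U-PEACE without a control group

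*Protocol article*

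**What the plan says.** In the Data Analytic Plan (Quantitative Analyses), the protocol article forms an RCI from each respondent's difference "from baseline to after treatment by the SE for each measure". A source is cited, but there is no formula, no mention of the SE of a difference, and no statement of which sign means improvement. The scores listed cover anxiety, depression, irritability, anxiety-related impairment and academic problems.

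The article then states that "RCI >1.96 indicates clinically significant change throughout the course of the program", "which would provide preliminary support that U-PEACE is impacting theoretical mechanisms" and participants' outcomes. The next paragraph adds: "Growth curve parameters will be used to categorize individual" participants' outcomes as deteriorated, unchanged, improved or recovered, judged against clinical cutoffs and RCIs. Mixed Methods Analyses merges these into responders (improved or recovered) and nonresponders.

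Under Recruitment, students qualify with "scores at or above the clinical cutoff for the Patient Health Questionnaire-9" or with "scores at or above the clinical cutoff for the Generalized Anxiety Disorder-7". Study Timeline and Aims describes the pilot case series as an open trial, and Study Strengths and Limitations places the value of RCIs in reading its early results.

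**The concern.** Three things are run together in the RCI paragraph.

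- **Divisor.** The 1.96 limit has its usual meaning only if the change is divided by the standard error of that change. The stated divisor reads as the error of a single measurement.
- **Label.** An RCI asks whether a change exceeds measurement error. Whether it matters clinically is a separate question, which the next paragraph recognises by using clinical cutoffs and by separating improved from recovered.
- **Inference.** Within-person change without a control group is taken as preliminary support for an effect on mechanisms and outcomes, in students admitted because they scored high on two of the scales being analysed.

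At stake are the individual response rates. They carry the case-series reading, they go to stakeholders, and they decide who counts as a responder for the interviews and joint displays.

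**Working it through.** **Inputs from the article.** RCI limit 1.96 (Quantitative Analyses). Reliability 0.87 for the PHQ-9 and 0.88 for the GAD-7, both adolescent self-report (Anxiety and Depression Symptoms). Entry at or above the PHQ-9 or GAD-7 cutoff (Recruitment).

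**Assumptions, because the article gives no figure.** 1.96 is meant as a two-sided 5% limit. Errors on the two occasions are independent and equally large. SD of each scale is 4 to 6 points. The cutoff lies at the 50th to 90th percentile of the source population.

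**Step 1: the limit.** The 97.5th percentile of the standard normal is 1.960. So 1.96 is a 5% limit for a statistic with variance 1 when nothing has changed.

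**Step 2: the divisor.** SEM = SD × √(1 − r). The SE of a difference is √(SEM² + SEM²) = √2 × SEM.

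- Change/(√2 × SEM) has variance 1: 5.0% flagged, 2.5% as improved.
- Change/SEM has variance 2: 2 × [1 − Φ(1.96/√2)] = 16.6% flagged, 8.3% as improved.

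The ratio is 16.6/5.0 = 3.3. Keeping the SEM as divisor would need a limit of 1.96 × √2 = 2.77.

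**Step 3: in points.** Change needed to pass the limit:

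| Scale (r) | SD | 1.96 × SEM | 1.96 × √2 × SEM |
|---|---|---|---|
| PHQ-9 (0.87) | 4 | 2.8 | 4.0 |
| PHQ-9 (0.87) | 5 | 3.5 | 5.0 |
| PHQ-9 (0.87) | 6 | 4.2 | 6.0 |
| GAD-7 (0.88) | 4 | 2.7 | 3.8 |
| GAD-7 (0.88) | 5 | 3.4 | 4.8 |
| GAD-7 (0.88) | 6 | 4.1 | 5.8 |

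**Step 4: regression to the mean on a selecting scale.** With no true change and selection on the same baseline score, the expected fall in SD units is (1 − r) × φ(c)/[1 − Φ(c)], where c is the cutoff as a z-score. At r = 0.88 and the 50th percentile this is 0.12 × 0.798 = 0.10. At r = 0.87 and the 90th percentile it is 0.13 × 1.755 = 0.23. Simulating 2 million normal score sets gives the share flagged as improved:

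| Setting | Divisor SEM | Divisor √2 × SEM |
|---|---|---|
| Screening score is baseline, stability 0.87 to 0.88 | 11% to 17% | 3.6% to 6.0% |
| Screening score is baseline, stability 0.70 (assumed), SEM from 0.88 | 27% to 42% | 16% to 27% |
| Separate baseline, stability 0.87 to 0.88 | 8.3% | 2.5% |

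Every simulated student is selected on the scored scale. The plan admits on either scale, so these figures are too high for a sample in which some students qualified only on the other one.

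**Step 5: what the RCI list covers.** The section on the original UP-A names emotion regulation and distress tolerance as the higher-order factors it targets. Distress tolerance is measured with its own scale but is not among the scores listed for the RCI.

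**The case against.** The strongest reply concerns the divisor. The article condenses a cited method into one sentence, the quantity being divided is a difference, and the phrase may be shorthand for the SE of that difference computed for each measure. The source cannot be checked here. On that reading the 16.6% and the lower point thresholds disappear, and only a wording correction remains. This stands as a limit on the divisor point; it does not touch the label or the inference.

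It is also fair that the claim is hedged as preliminary, that cutoffs enter in the next paragraph, and that regression to the mean acts directly only on the self-reported PHQ-9 and GAD-7, not on caregiver reports, irritability, impairment or academic problems. Interviewees are to be split evenly between responders and nonresponders, so a higher responder rate would not shift that balance, although it would change who falls on each side.

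A reader might infer more than the article supports:

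- **That every output is biased towards showing change.** A divisor that is too small also inflates the deteriorated category. Classifying from growth-curve parameters could involve estimates shrunken towards the arm mean, but the article does not say so, and the direction would vary. With a true-change SD of 3, shrinkage of 0.49 and a threshold of 5 points (all assumed), a mean improvement of 8 gives 92% responders from shrunken estimates against 76% from observed scores; a mean of 3 gives 17% against 32%. Using model-based or observed scores is a trade-off, not an error.
- **That a large share of improvement would be artefact.** The high rates in Step 4 need a retest stability well below the reported 0.87 to 0.88.
- **That no mechanism is measured.** Irritability is scored with the Affective Reactivity Index, and the Introduction names emotional reactivity as underlying these disorders. Only the absence of distress tolerance can be stated.

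**Conclusion.** The paragraph is wrong as written and should be corrected before individual response rates are reported.

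- **Divisor (conditional).** If the SE is each measure's SEM, unchanged students are flagged at 16.6% rather than 5%, and as improved at 8.3% rather than 2.5%. This needs only equal, independent errors; the point thresholds also need an assumed SD. If the SE of the difference is meant, there is no inflation and the text is merely unclear.
- **Label (unconditional).** RCI >1.96 is reliable change. Calling it clinically significant conflicts with the cutoff-based categories that follow.
- **Inference (unconditional).** Uncontrolled RCIs in students selected on high scores cannot support an effect of U-PEACE. The size of the regression to the mean is uncertain: it depends on SDs, retest stability and whether screening scores serve as baseline, none of which the article settles.

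The multilevel comparison of U-PEACE with SAU does not use RCIs and is not affected. The damage is confined to individual response rates and the categories built on them.

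**What to change.** 1. Define RCI = (baseline − after treatment)/(SEM × √2), with SEM = SD × √(1 − r), and give the source of r and SD for each measure and informant. Higher scores are worse on the listed measures, so positive values then mean improvement.
2. Call |RCI| >1.96 reliable change.
3. Require a crossing of the clinical cutoff as well before using the terms clinically significant or recovered.
4. In the randomised trial, report the RCI categories in both arms with the difference in proportions.
5. Limit case-series RCIs to description and remove the statement that they support an effect on mechanisms or outcomes. Say whether screening scores serve as baseline. The Distress Tolerance Scale could be added to the list, also descriptively.

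These are changes of formula and wording and need no new data. The cost is that fewer students will be labelled improved.

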**Figure 2 figure2:**
[figure not shown]
Anticipated CONSORT (Consolidated Standards of Reporting Trials) diagram for the Unified Protocol for Transdiagnostic Treatment of Emotional and Academic Challenges in Education (U-PEACE) study. The diagram includes information from the anticipated participant allocation. At the completion of the study, a final CONSORT diagram will be presented with study results that include final data regarding recruitment and retention of participants. SAU: service as usual.

While the research team will be exploring the feasibility of telehealth-delivered U-PEACE, most U-PEACE sessions are expected to be delivered in person, during lunchtime, and in group format. Students who are enrolled in U-PEACE will be permitted to access additional primary, medical, and mental health care services within the school clinics throughout their participation in U-PEACE. The original UP-A typically takes place over 12 to 16 sessions. Thus, it was anticipated that U-PEACE would eventually contain a session count in this range. Each U-PEACE group will ideally have approximately 4 to 8 students enrolled in it at one time, as well as 1 to 2 clinicians in training who serve as program leaders for the group. At the beginning of the U-PEACE group, adolescent participants will receive a binder of U-PEACE session and homework worksheets that they can reference when learning and reviewing the program content. Adolescents will be expected to bring their binders to every U-PEACE session and practice skills learned in the group as homework between program sessions. In addition to U-PEACE binders, adolescents will also be given a caregiver session summary sheet to provide to their caregivers; these summary sheets are intended to keep caregivers informed about skills their adolescents are learning in U-PEACE.

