#### Sample Size and Power Analysis

The recommended size for a single focus group is 6 to 8 participants for sufficient diversity of opinions and to encourage discussion [97,98]. Consequently, we will seek to have at least 5 participants included in each adolescent, caregiver, teacher, school administrator, and school mental health provider focus group, for 25 participants at the initial adaptation phase, to gather sufficient data to inform the modifications to the UP-A (aim 1), rather than powering for specific effects. In addition, qualitative feedback will be obtained following the pilot case series and RCT (aims 2 and 3) to inform implementation outcomes (aim 4). All participants in the pilot case series will be invited to participant in the qualitative feedback interviews, and the same recommendation size of 25 participants will be used for the RCT qualitative feedback interviews. Power calculations for the nested multilevel models were conducted using Optimal Design 3.1 [99] to identify the minimum number of participants needed to participate in the RCT across 7 treatment groups with 5 assessment points. We estimated power using intraclass correlation coefficient (ICC) values of 0.01 based on recent effectiveness trials with a similar transdiagnostic intervention [100] and a more conservative estimate of 0.10. With an estimated sample size of 63 adolescents, the sample would have sufficient power (0.80) to detect an effect size of *d*=0.94 (ICC=0.01) or 1.21 (ICC=0.10), which are smaller effect sizes (*d*=1.25) than those observed in an UP-A RCT [43].

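### The outcome model enters U-PEACE provider beside treatment condition and names no therapy-group level, so the condition coefficient depends on an unstated coding and its error omits group variance

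*Protocol article*

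**What the plan says.** All of the model text is in one paragraph of the Quantitative Analyses section of the protocol article.

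- Nesting: "nesting of repeated measures (3 or 4 time points, depending on the measure) within participants, who are further nested within study conditions". No therapy-group level is named.
- Covariates: "School and U-PEACE group provider or providers will be included as predictors of intercept and slope to control for environmental differences between the groups".
- Arm: "Treatment condition (ie, U-PEACE or SAU) will be entered as a predictor of the level 2 growth curve parameters (intercepts and slopes").

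The Study Intervention section describes delivery. "Each U-PEACE group will ideally have approximately 4 to 8 students enrolled in it at one time", with "1 to 2 clinicians in training who serve as program leaders for the group". The Comparison Condition section gives SAU students school clinic services and a short weekly contact with study staff. They have no U-PEACE group and no U-PEACE leader.

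The Sample Size and Power Analysis section does allow for clustering: "We estimated power using intraclass correlation coefficient (ICC) values of 0.01", with 0.10 as the conservative alternative, across 7 treatment groups and 63 adolescents.

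**The concern.** There are two linked faults in what the article fixes.

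First, provider is not a covariate that varies in both arms. It is defined only under U-PEACE and is part of how the intervention is delivered, so it is not an environmental difference that can be adjusted away between arms. If every provider has an indicator, these indicators add up to the U-PEACE indicator, on the intercept and again on the slope. What the condition coefficient then estimates depends on how the software or the analyst breaks the tie.

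Second, students treated together share a group and its leaders. That variation belongs in the error of the arm comparison. The article counts clustering when it sizes the trial and names no such level when it analyses it. Study condition cannot fill the gap, because it is a two-category fixed contrast and not a sample of units.

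The same models are to serve symptoms, academic outcomes, diagnostic measures and mechanisms, so the fault reaches every between-arm result.

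**Working it through.** **Inputs from the article.** N = 63; 7 groups in the power calculation; ICC 0.01 and 0.10; stated detectable d = 0.94 and 1.21 at power 0.80; U-PEACE groups of about 4 to 8; 3 schools.

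**Assumptions, not in the text.** Two-sided alpha 0.05; 32 U-PEACE and 31 SAU students; no dropout; 2 to 7 providers; 4 to 7 U-PEACE groups; SAU students independent.

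**1. The article's own power figure.** Take 7 random clusters of 63/7 = 9 students, with SE(d) = √{4[ICC + (1 − ICC)/9]/7} and a noncentral t on 7 − 2 = 5 df.
- ICC 0.01: SE = 0.262, and power at d = 0.94 is 0.816.
- ICC 0.10: SE = 0.338, and power at d = 1.21 is 0.814.

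Both are close to 0.80. With no clustering (31.5 per arm) the detectable d would be 0.71. The power calculation therefore treats groups as random clusters.

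**2. Aliasing.** Take 4 providers, 3 schools and condition, on intercept and slope. Columns = 2 × (1 intercept + 1 condition + 4 providers + 2 schools) = 16, and the rank is 14. One redundancy falls on the intercept and one on the slope. The intercept part alone, without school, is one rank short for any number of providers: 2 providers give 4 columns and rank 3; 7 give 9 columns and rank 8.

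**3. What a reference provider does.** With k equal providers, the condition coefficient compares 32/k students with 31, so the ratio to the arm-only standard error is √(k/32 + 1/31) / √(1/32 + 1/31).
- k = 2: 0.308/0.252 = 1.22
- k = 4: 0.397/0.252 = 1.57
- k = 7: 0.501/0.252 = 1.99

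If provider columns are centred within U-PEACE and set to 0 for SAU, the coefficient is the average arm effect and its standard error is essentially the arm-only one.

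**4. Group variance left out.** For an arm-only test at 1:1 with groups of m, true SE / model SE = √{[1 + (m − 1)ICC + 1]/2}, and type I error ≈ 2[1 − Φ(1.96/ratio)].
- ICC 0.01: m = 4 gives ratio 1.007 and 5.2%; m = 8 gives 1.017 and 5.4%.
- ICC 0.10: m = 4 gives ratio 1.072 and 6.8%; m = 8 gives 1.162 and 9.2%.

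**5. Simulation under no average arm effect.** There were 20,000 runs per row, with one outcome per student (a simplification of the growth model) and ICC 0.10. Entries are rejection rates of the nominal 5% test.

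| Groups | Providers | Arm only | Provider centred | Reference provider |
|---|---|---|---|---|
| 4 | 2 | 8.9% | 9.2% | 10.7% |
| 4 | 4 | 9.2% | 9.8% | 12.6% |
| 7 | 3 | 7.2% | 7.4% | 8.6% |
| 7 | 7 | 7.3% | 7.7% | 8.7% |

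At ICC 0.01 every entry lies between 5.2% and 5.6%. The reference-provider column counts a rejection as false because the average arm effect is zero. The larger standard error under that coding is still too small for the true sampling variation.

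**The case against.** The strongest reply has four parts.

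- **Coding is left open.** The article says neither fixed nor how provider is coded, and a condensed article may leave coding to an analysis plan that is not shown. A reader might infer from the aliasing that the arm effect cannot be estimated at all. That is not so: the average U-PEACE minus SAU contrast stays estimable, and centred coding delivers it at no cost in standard error. The ratios of 1.2 to 2.0 apply only to the raw coefficient under reference coding. What stands is that the article fixes provider and condition side by side and states none of the coding that would make this safe.
- **Provider terms may stand in for groups.** If each group has its own leaders, provider terms act as fixed group effects, a recognised device when clusters are few. But inference is then confined to the groups observed, and between-group variance is still missing from the error of the average arm effect, as the centred column shows.
- **The ICC drawn from earlier trials is 0.01.** At that value the understatement is trivial. A reader might infer a general inflation of the error rate, but it is material only towards the article's conservative 0.10.
- **The seven groups are not shown to be therapy groups.** The power figure reproduces with 7 clusters of 9 across all 63 students. It does not with 7 groups of 4.5, which gives detectable d of 1.27 and 1.45. The power section therefore shows that group clustering was counted, but not that the U-PEACE arm has seven groups.

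The phrase "participants, who are further nested within study conditions" could be read as a random level for condition. The same paragraph enters condition as a predictor, so loose wording is the likelier reading. No therapy-group level is stated either way.

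**Conclusion.** The concern holds in a limited form. The stated model places provider beside condition although provider exists in one arm only. The condition coefficient is therefore aliased under full coding, or is one provider versus SAU under reference coding, unless a coding is chosen that the article does not give. This part does not depend on the ICC.

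The model also omits the group variance that the article's own power calculation includes. At ICC 0.01 the effect on type I error is negligible (5.2% to 5.4% for an arm-only test). At ICC 0.10 it is about 7% with seven groups to 9% with four groups of 8 for an arm-only test, about 7% to 10% with centred provider terms, and about 9% to 13% with a reference provider.

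These sizes rest on the assumed allocation and the assumed numbers of providers and groups. They also treat SAU students as independent, which is approximate because usual services may include group CBT. The fault lies in what the article specifies, so it is not a detail left to an analysis plan.

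**What to change.** In the Quantitative Analyses section:

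1. Remove provider as a predictor alongside condition. Keep school and condition as fixed effects.
2. Fit a partially nested model: repeated measures within students, plus a random effect for therapy group (or for leader, if leaders run several groups) that acts in the U-PEACE arm only. Put it at least on the intercept, and on the slope if it can be estimated.
3. Use Satterthwaite or Kenward-Roger degrees of freedom.
4. Delete the clause that nests participants within study conditions.
5. Describe variation between providers within the U-PEACE arm only.

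This needs wording and code but no new data. The statistical cost is real. As a single-time-point guide, take 4 groups of 8 at ICC 0.10. The arm variances are (1 + 7 × 0.10)/32 = 0.0531 on 3 df and 1/31 = 0.0323 on 30 df. The Satterthwaite df is 0.0854² / (0.0531²/3 + 0.0323²/30) ≈ 7.5, against 61 for the unclustered test. Seven groups lose less, but random slopes remain hard to estimate with 4 to 7 groups, so the fallback to a random intercept should be written down in advance.
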